#### 4.2.1 Revised and corrected Stage 2 power and precision calculations

Assumptions underlying the following Stage 2 power calculations include the following:

1. 5% of patients are ineligible for the intervention package (pregnancy, lactation, severe malaria, age <6m (Indonesia) or <1 yr (PNG)).
2. The impact on the risk and rate of infection will be the same across different endemic sites.
3. The mean baseline risk of *P. vivax* recurrence at 6 months is 20%
4. Loss to follow-up in both groups is 10%
5. Alpha = 0.05

During the 12-month pre-implementation period, a total of **17,160** patients with *P. vivax* (mono or mixed infections) presented to the ten study clinics (see Table 1). Assuming 5% of patients are ineligible for enrolment due to pregnancy, lactation or age under 6 months (Indonesia) or 12 months (PNG), this gives an estimated maximum number of patients eligible for recruitment into Stage 2 of **16,300**.

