**Table 1 Number of patients with vivax malaria attending the ten study clinics in last 12 months**

| Clinic name     | Country   | Locality               | Estimated total number of P. vivax episodes per year | Estimated maximum recruitment in SCOPE Stage 2 (95%) |
|-----------------|-----------|------------------------|-------------------------------------------------------------|------------------------------------------------------|
| Timika          | Indonesia | Timika, Southern Papua | 3173                                                        | 3014                                                 |
| Bhintuka        | Indonesia | Timika, Southern Papua | 1164                                                        | 1106                                                 |
| Pasar Sentral   | Indonesia | Timika, Southern Papua | 4937                                                        | 4690                                                 |
| Wania           | Indonesia | Timika, Southern Papua | 3681                                                        | 3497                                                 |
| Tanjung Leidong | Indonesia | North Sumatra          | 500                                                         | 475                                                  |
| Hanura          | Indonesia | Lampung                | 450                                                         | 428                                                  |
| Baro            | PNG       | West Sepik             | 417                                                         | 396                                                  |
| Mugil           | PNG       | Madang                 | 1044                                                        | 992                                                  |
| Napapar         | PNG       | East New Britain       | 412                                                         | 391                                                  |
| Wirui           | PNG       | East Sepik             | 1382                                                        | 1313                                                 |
| Total           |           |                        | 17,160                                                      | 16,302                                               |

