| 0.5                                                               | 8,150                                   | 135.8                                                           | 12.22                                  | 123.58                                                            | 63.2%                                         |

**Example STATA code:** power pairedm 135.8 111.36, sddiff(15) n(10) alpha(0.05).

Based on previous estimates, 60% of cases of *P. vivax* malaria seen at each clinic are due to relapse and therefore preventable with improved radical cure. We predict the intervention package will reduce the individual risk of relapse by 30%. With anticipated recruitment of 70% of eligible patients, the total predicted sample size in Stage 2 would fall to **11,410** patients receiving primaquine over 12 months of enrolment. Based on this lower predicted enrolment and using the assumptions as above, the predicted absolute reduction in incidence at each clinic would be 17.11 cases per month  $((135.8 \times 0.6) \times 0.3 \times 0.7)$  and resultant power to detect this difference would be **89.3%**.

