## 4.2.2 Original power and precision calculations – now superseded

**Indonesia and PNG combined study**

The Stage 2 implementation study will be conducted at ten health facilities across Indonesia and Papua New Guinea. Based on prior surveillance, we estimate that over 18 months, these health facilities will enrol approximately 16,300 patients with vivax malaria. Improved radical cure of *P. vivax* malaria is expected to reduce the risk of subsequent relapse and therefore reduce the overall incidence of vivax malaria. Across the 10 health facilities, a mean of 91 patients with vivax malaria are expected to be seen each month, 60% ( $n=54.3$ ) of which are predicted to be relapses and therefore feasibly preventable. Assuming that the implementation package in Stage 2 will reduce relapses by 30%, the monthly incidence of *P. vivax* malaria is expected to fall by 16.3 (17.9%) to 74.7 cases per month. With a two-sided alpha of 0.05 and a predicted standard deviation of the mean variation in monthly numbers of vivax malaria of 15 episodes per month, our study would achieve 86% power to detect an 18% reduction in monthly *P. vivax* malaria incidence. Furthermore, assuming 70% of patients receive all components of the implementation package correctly, this sample size will give a 95% confidence interval for the true proportion of  $\pm 0.70\%$ . If 1% of patients are predicted to have a treatment-limiting haemolytic event, this sample size will be powered to determine the true proportion within  $\pm 0.15\%$ .

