facilities, a mean of 77 patients with vivax malaria are anticipated each month, 60% ( $n=46.3$ ) of which are predicted to be relapses and are therefore preventable. Assuming that the implementation package in Stage 2 will reduce relapses by 30%, the monthly incidence of *P. vivax* malaria is expected to fall by 13.8 (17.9%) to 63.2 cases per month. The PNG arm of the study would retain 80% power to detect a 42% overall reduction in incidence following implementation of the interventions. Furthermore assuming 70% of patients receive all components of the implementation package correctly, this sample size will give a 95% confidence interval for the true proportion of  $\pm 1.21\%$ . If 1% of patients are predicted to have a treatment-limiting haemolytic event, this sample size will be powered to determine the true proportion within  $\pm 0.26\%$ .

Results of the power calculations for the effectiveness endpoints provided above have been confirmed using numerical simulations. A total of 1000 simulated datasets from 10 health facilities, with 18 months of observations and 91 infections per month (in the pre-intervention phase) were generated. Between health-facility variation in the outcome was based on an intra-cluster correlation coefficient of 0.1, and within health-facility variation was assumed to have a standard deviation of the mean variation in monthly numbers of vivax malaria of 15 episodes per month.

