The model will include time (month) as a continuous variable, a binary variable for the implementation intervention (see (a) and (b) above), an interaction between elapsed time (since implementation) and the implementation, seasonal variation in malaria (captured using splines), adjusted for potential time-varying confounding variables including large scale malaria control activities outside of the SCOPE study and unexpected antimalarial stock outages, and allowing for a random effect for intercept to account for clustering by health facility site (Turner SL et al. 2021).

For the effectiveness outcome S2.SE15, monthly incidence of symptomatic *P. vivax* malaria will be calculated using clinic catchment populations provided by health facilities (or if not available, the most recent census). Incidence rate ratios (IRRs) (95% CIs) for the intervention effect will be estimated from a negative binomial regression model fitted to the monthly aggregated data.

**Figure 2.** Example impact model for the implementation package on the effectiveness outcome measure S2.SE15 (incidence of symptomatic *P. vivax* malaria infections). An impact model with an immediate change in level and slope. While immediate level change is allowed to occur in this model at the time of implementation, the estimand of interest with regards to level change will be calculated 6 months after implementation (at 12 months) relative to the implementation timepoint (at 6 months).

[figure not shown]

For comparison of outcomes S2.SE16 (the proportion of febrile patients with asexual *P. vivax* parasitaemia by microscopy) and S2.SE14 (the proportion of patients with severe anaemia (haemoglobin < 7 g/dl), determined from cross-sectional surveys in the pre- and post-implementation periods), prevalence ratios (95% CIs) for the intervention effect will be estimated from log-binomial regression models, and if there are convergence issues, Poisson regression with robust variance will be performed (Barros AJD & Hirakata VN 2003).

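### The 89.3% power for S2.SE15 is for a paired t-test the plan does not use, with an SD of differences too small for the Table 1 clinics at 70% recruitment and above

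*SAP*

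**What the plan says.** Section 4.2.1 predicts a reduction of 0.6 × 0.3 × recruitment. At 70% recruitment that is 12.6%, or 17.11 cases per clinic per month from a mean of 135.8. Table 2 gives power of 99.5, 98.4, 95.5, 89.3, 78.6 and 63.2% for recruitment of 100% down to 50%. The example code is "power pairedm 135.8 111.36, sddiff(15) n(10) alpha(0.05"). Assumption 2 of the same section reads: "The impact on the risk and rate of infection will be the same across different endemic sites".

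The SD of 15 first appears in Section 4.2.2, which is marked as superseded and uses a mean of 91 a month. There it is "a predicted standard deviation of the mean variation in monthly numbers of vivax malaria of 15 episodes per month". The simulation check at the end of that section describes it differently: "within health-facility variation was assumed to have a standard deviation of the mean variation in monthly numbers of vivax malaria of 15 episodes per month". That check used 91 infections a month over 18 months.

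Section 9.2 plans a segmented regression of monthly clinic data with time, intervention and interaction terms, seasonal splines and a random clinic intercept. "Incidence rate ratios (IRRs) (95% CIs) for the intervention effect will be estimated from a negative binomial regression model". The two effects of interest are the level change at 6 months and the slope change.

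**The concern.** Table 2 is presented as the corrected power for the first-listed effectiveness endpoint. Three things do not fit.

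- **The SD of differences.** The effect is built as a percentage of each clinic's cases, and Table 1 shows a twelve-fold range of clinic volumes. Absolute reductions must then differ widely between clinics. That spread is part of the SD of differences and has to fit inside the 15.
- **The carry-over.** The mean was corrected from 91 to 135.8 and the SD was left alone.
- **The test.** A paired t-test on clinic means spends no information on trend, slope or season. The planned model does.

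If the final estimate is imprecise, readers may use 89.3% to judge whether a null result counts against the package. The documents do not show that the planned analysis has that power.

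**Working it through.** **1. Reproducing Table 2.** This is a two-sided paired t-test with n = 10, df = 9, alpha 0.05 and critical value 2.262. The noncentrality is d / (15/√10). At d = 17.11 it is 17.11 / 4.743 = 3.607, and the noncentral t gives 89.3%. All six rows match to the printed decimal.

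**2. SD of reductions implied by Table 1.** The maximum-recruitment column divided by 12 gives 251.2, 92.2, 390.8, 291.4, 39.6, 35.7, 33.0, 82.7, 32.6 and 109.4 cases a month (mean 135.85, SD 128.45). With the same relative effect f = 0.18 × recruitment at every clinic, the SD of the reductions is f × 128.45. At 70% the reductions run from 4.1 to 49.2 cases a month.

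| Recruitment | f | SD of reductions | SD in Table 2 | Stated power |
|---|---|---|---|---|
| 100% | 0.180 | 23.1 | 15 | 99.5% |
| 90% | 0.162 | 20.8 | 15 | 98.4% |
| 80% | 0.144 | 18.5 | 15 | 95.5% |
| 70% | 0.126 | 16.2 | 15 | 89.3% |
| 60% | 0.108 | 13.9 | 15 | 78.6% |
| 50% | 0.090 | 11.6 | 15 | 63.2% |

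The SD of 15 is too small in the top four rows before any random variation is added. In the bottom two it is not contradicted by Table 1 alone.

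Putting only this SD into the SAP's formula, recruitment cancels. The noncentrality is (135.85 / 128.45) × √10 = 3.344, and power is 84.4% in every row.

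An equal absolute fall of 17.11 at every clinic does not rescue the 15. At the smallest clinic it would be 17.11 / 32.6 = 52%, against the 12.6% that the inputs allow.

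**3. The carry-over.** The superseded calculation has d = 16.3 and SD 15, a ratio of 1.09; it reproduces at 86%, as stated. At full recruitment the corrected calculation has d = 24.44. If the SD grew in proportion to the mean, it would be 15 × 135.8 / 91 = 22.4, and the ratio would again be 24.44 / 22.4 = 1.09. The Section 4.2 note that power had been underestimated therefore depends on holding the SD at 15.

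**4. The planned model.** The following are my assumptions, not SAP values: 12 + 12 months at all ten clinics, Table 1 volumes, clinic intercepts, linear time, level and slope terms, one annual harmonic per country in place of the splines, no autocorrelation, and an IRR at month 6 of 1 − 0.126 = 0.874. The approximate power is Φ(0.1347/SE − 1.96), where 0.1347 = −ln 0.874 and SE comes from the negative binomial information matrix.

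| Extra-Poisson CV (assumed) | SE of log IRR | Power |
|---|---|---|
| 0 (Poisson) | 0.040 | about 92% |
| 7% | 0.056 | about 67% |
| 11% | 0.071 | about 48% |
| 16.5% | 0.092 | about 31% |

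Without seasonal terms the same CVs give about 99, 88, 70 and 47%. The choice of month origin moves these figures by a few points. The 16.5% is 15/91, the SAP's SD relative to its old mean.

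**5. The simulation check.** It used the superseded mean. It also states: "Between health-facility variation in the outcome was based on an intra-cluster correlation coefficient of 0.1". With a within-clinic SD of 15, that is a between-clinic SD of 15 × √(0.1/0.9) = 5, whereas the Table 1 volumes have an SD of 128. It does not validate the revised figures.

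**The case against.** Several replies are fair, and some of them stand.

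- **The level SD of 128 cancels in a paired test.** True. A reader might infer that 15 is a between-clinic SD which Table 1 refutes outright. It is not: the code enters it as the SD of differences. The conflict arises only through a common relative effect at unequal clinics, and at 70% recruitment it is modest (16.2 against 15).
- **Power is not capped at 84% in general.** Also true. That figure belongs to the SAP's formula, which treats the clinics as a random normal sample. With ten fixed sites and no noise, the paired t is always 3.34 against a critical value of 2.26, so power is 100%. If 15 is independent monthly noise averaged over 12 + 12 months, the noise SD of the difference is 15 × √(2/12) = 6.1, and simulated power at the fixed sites is 98%.
- **Adding 15 in quadrature to the clinic spread is not warranted.** It gives 59% at 70% recruitment, or 42% if 15 is first scaled to the new mean. Both require the added SD to be pure noise in the 12-month difference, and the SAP nowhere says that. I do not rely on either figure.
- **A log-link model handles a common relative effect well.** It does, so unequal absolute reductions are no problem for the planned analysis. This does not rescue Table 2, because Table 2 is not the power of that model.
- **S2.SE15 is secondary and is reported with a 95% CI.** True. No decision rule hangs on Table 2, and the primary endpoint has its own precision statement.

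**Conclusion.** The point holds in limited form. The arithmetic of Table 2 is right for its inputs. Its SD of 15 conflicts with the SAP's own volumes and effect assumption in the 70% to 100% rows, was not re-justified when the mean changed, and feeds a test that is not planned for S2.SE15. Within the SAP's formula, clinic spread alone takes the 89.3% to 99.5% figures down to 84%.

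The power of the planned month-6 IRR is not given. Under the assumptions above, 89.3% would need close to Poisson variation, and modest extra variation takes the power well below it. A reader might conclude that the study is underpowered for incidence. The documents do not support that either, since site-month dispersion is not stated and the range runs from about 92% down to about 31%. No power is given for the slope change at all. The primary endpoint is unaffected.

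**What to change.** - Replace Table 2 and the 89.3% with power simulated from the planned S2.SE15 model, for both the month-6 level change and the slope change.
- Use the Table 1 clinic means, a common rate ratio of 1 − 0.18 × recruitment, the planned seasonal splines, and site-month dispersion and autocorrelation estimated from the existing pre-implementation series.
- State the slope change assumed, since the SAP predicts none.
- Qualify the Section 4.2 note so that it says power was underestimated only with the SD kept at 15.
- State that the simulation check in Section 4.2.2 applies to the superseded inputs.

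The cost is one simulation and a few lines of SAP text. The stated power may become less favourable. Study conduct and the primary endpoint do not change.

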### **S2.SE17 - Reduction in individual risk of recurrence**

The power estimates for detecting a reduction in the individual risk of recurrence of *P. vivax* within 6 months from an anticipated study enrolment of **11,410 patients** are presented in Table 3. The number of patients included in the pre-implementation and implementation stages are assumed to be equal (ie a total of 22,820 patients pre and post implementation).

**Table 3 – Power to detect reduction in the risk of recurrence**

| Proportion of eligible P. vivax malaria patients recruited | Eligible patients over 12 months period | 30% Risk Reduction (HR 0.7) | 20% Risk Reduction (HR 0.8) | 10% Risk Reduction (HR 0.9) |
|-------------------------------------------------------------------|-----------------------------------------|-----------------------------|-----------------------------|-----------------------------|
| 1                                                                 | 16,300                                  | 100%                        | 100%                        | 98%                         |
| 0.9                                                               | 14,670                                  | 100%                        | 100%                        | 97%                         |
| 0.8                                                               | 13,040                                  | 100%                        | 100%                        | 95%                         |
| 0.7                                                               | 11,410                                  | 100%                        | 100%                        | 92%                  |
| 0.6                                                               | 9,780                                   | 100%                        | 100%                        | 88%                         |
| 0.5                                                               | 8,150                                   | 100%                        | 100%                        | 82%                         |

**Example STATA code:** artsurv, edf0(0.2) hr (1,0.7) fp(1) n(22,820) alpha(0.05) nperiod(1) tunit(2) lg(1 2) ldf(0.1;0.1).

A sample size of 11,410 (70% eligible patients) would provide **92% power** to detect a minimum 10% reduction in risk of recurrence and 100% power to detect a 30% reduction in risk of recurrence.

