### 3.1.2. Stage 2 – Large-scale implementation and feasibility study

Stage 2 of the study will be a feasibility study conducted at 10 community health-care facilities: 6 sites in Indonesia and 4 sites in Papua New Guinea. The primary purpose of Stage 2 is to determine the feasibility and cost-effectiveness of the complete revised case management initially studied in Stage 1. Robust Pre-Implementation malarimetric surveillance for a minimum of 12 months along with quantitative surveys of baseline operational metrics and costs will be followed by coordinated introduction of the revised case management across all study health facilities and a minimum of a further 12 months of surveillance – creating an interrupted time series comparing the endpoints listed in section 2.2.2.

During Stage 2 study procedures will be the same as those for Stage 1, except that the procedures will be performed by routine healthcare staff. All patients will be reviewed by community health workers (CHW) at home 3 days after starting PQ. The review may also take place at the health facility, if the patient presents there. Exceptionally, the follow-up may also take place via a phone call if the patient is not physically reachable at home. The CHW will complete a signs and symptom checklist to detect early indicators of haemolysis or other AESI. Patients with signs of haemolysis or other AESI will have their primaquine ceased and will be referred to the health facility for medical review. Patients tolerating their medication will be encouraged to adhere to a full (7 or 14 days) course of treatment. Safety outcomes occurring between day 3 and end of treatment will be detected passively by community-based health workers, study health facilities and regional hospitals.

Continuous surveillance and pharmacovigilance over the entire study period will enable interrupted time-series analyses of malarimetric indices (see section 2.2.2).

Figure 1 presents the study schedule for the baseline data, pre-implementation stage, and stages 1 and 2.

**Figure 1. Study overview**[figure not shown]

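### Table 3's 92% power for a 10% reduction in S2.SE17 uses a yearly episode count as the number of distinct patients; counting each patient once gives about 86-88%, and less if follow-up is truncated

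*SAP*

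**What the plan says.** All places are in the SAP.

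- **Table 1 (4.2.1).** The column totalling 17,160 is headed as "episodes per year". The table's title, its footnote and the text above it call the same figure patients. Removing 5% as ineligible gives 16,300.
- **Table 2 and the text on S2.SE15.** The 16,300 becomes a mean of 135.8 cases per clinic per month (16,300 / 12 / 10). At 70% recruitment, 11,410 is described as "patients receiving primaquine over 12 months of enrolment".
- **S2.SE17 and Table 3.** The same counts become subjects in a survival calculation: "The number of patients included in the pre-implementation and implementation stages are assumed to be equal", for a total of 22,820. The conclusion reads "A sample size of 11,410 (70% eligible patients) would provide" 92% power for a 10% reduction.
- **Assumptions in 4.2.1.** "recurrence at 6 months is 20"%, and "Loss to follow-up in both groups is 10"%. The example code carries the loss but has a single period and no staggered entry: "nperiod(1) tunit(2) lg(1 2) ldf(0.1;0.1").
- **3.1.2.** Post-implementation surveillance is "a minimum of a further 12 months of surveillance".
- **9.2.** S2.SE17 is a patient-level survival analysis of all patients eligible for primaquine, with a shared frailty for health facility. The section gives neither a rule for repeat episodes nor a censoring date.

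**The concern.** One number serves as two different things. In Table 2 it is case incidence, so a patient who returns three times counts three times. In Table 3 it is the number of independent subjects, so each patient should count once. Both can be right only if nobody recurs within the year, yet recurrence is the endpoint and is put at 20% within 6 months. No deduction is made, so Table 3 expects more events than the stated numbers can supply.

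A second omission points the same way. Enrolment is spread over 12 months and only 12 months of surveillance is guaranteed. On that minimum, patients entering in the second half of the year cannot be watched for 6 months, and Table 3 makes no allowance for this.

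At stake is the power quoted for the smallest effect that the plan considers on its individual-level before-and-after effectiveness endpoint.

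**Working it through.** **Inputs.** From 4.2.1: 20% risk at 6 months, 10% loss per group, alpha 0.05 (taken as two-sided), HR 0.9, 11,410 per period. From 4.2.1 and 3.1.2: 12 months of enrolment and at least 12 months of surveillance.

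**Step 1: reproduce Table 3.** Per 6-month period, the event hazard is h = -ln(0.8) = 0.2231 and the loss hazard is l = -ln(0.9) = 0.1054. The probability of an observed event is h/(h+l) × [1 - exp(-(h+l))], which is 0.1902 before implementation and 0.1730 after it (with 0.9h).

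Events: 11,410 × 0.1902 = 2,170 and 11,410 × 0.1730 = 1,974, together 4,144.

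Power = Φ(|ln 0.9| / √(1/2,170 + 1/1,974) - 1.96) = Φ(0.1054/0.0311 - 1.96) = 92.3%.

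The six HR 0.9 rows come out at 98.2, 97.0, 95.2, 92.3, 88.0 and 81.7%, against the printed 98, 97, 95, 92, 88 and 82%. Table 3 therefore assumes 11,410 distinct subjects per period, 10% loss and no end-of-surveillance cut.

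**Step 2: convert episodes to patients.** The SAP gives no episodes-per-patient ratio, so this step is an assumption: a constant monthly episode rate and a constant recurrence hazard of 0.2231/6 = 0.0372 per month. The share of a 12-month window's episodes that follow an earlier one by the same patient is:

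- hazard continuing all year: 1 - (1 - e^(-12×0.0372))/(12×0.0372) = 19.3%, leaving 9,204 patients;
- recurrence stopping at 6 months: ½ × 10.4% + ½ × 20% = 15.2%, leaving 9,677 patients.

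The same N is used in both periods.

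| Distinct patients per period | Events (pre + post) | Power, HR 0.9, full follow-up |
|---|---|---|
| 9,677 | 1,841 + 1,674 | 87.7% |
| 9,204 | 1,751 + 1,592 | 86.0% |

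A harsher ratio of 1.36 episodes per patient (12-month risk 1 - 0.8² = 36%) leaves 8,390 patients and about 83%.

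**Step 3: add administrative censoring at 12 months.** With entry at month t, follow-up is min(6, 12 - t). Under even entry, the mean event probabilities fall to 0.1452 (pre) and 0.1319 (post).

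| Distinct patients | Post period cut | Both periods cut |
|---|---|---|
| 9,677 | 82.5% | 77.8% |
| 9,204 | 80.5% | 75.7% |

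Taking the first episode in the period as index moves entry slightly earlier and gives 82.8% and 81.5% (post cut) or 78.5% and 77.6% (both cut). The ranges are therefore about 80-83% and 76-79%. With 6 months of surveillance after the last index visit, the results return to Step 2.

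**Step 4: the other columns.** With both periods cut and 9,204 patients, power is above 99.9% for HR 0.8 and 100% for HR 0.7.

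**The case against.** The strongest reply is that Table 3 computes correctly what it was given. All six rows reproduce, so the fault lies in the inputs and not in the arithmetic. That is right.

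A reader might go further and infer that the plan's own inputs put the power at 78-83%. They do not. That range needs an episodes-to-patients ratio that the SAP does not give. It also needs surveillance to stop at 12 months, which is a stated minimum, and its lower end needs pre-period patients to be censored at implementation, which is nowhere stated. Nor does Table 3 assume that everyone completes 6 months: the 10% loss is in both the assumptions and the code. Nor is 92% the only power stated: Table 3 has 18 values, and the sentence that gives the 92% also gives 100% for a 30% reduction.

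The effect that the plan predicts is also larger than 10%. A 30% cut in relapse, with 60% of cases being relapses, is an 18% fall (HR 0.82). Power for that stays at 99.8-99.9% with both corrections and both periods cut. Diluted by 70% recruitment to 12.6% (HR 0.874), it is 92-93%.

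Finally, 9.2 analyses all eligible patients, not only the 70% recruited. Applying Step 2 to 16,300 gives 13,148-13,825 patients per period and, for HR 0.9, 95-96% with full follow-up or 89-90% with both periods cut, before any dilution of the effect. So 11,410 may not be the right starting N.

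These points limit the consequence. They do not restore 92% as the power for the 11,410 to which it is attached. If every episode were instead a new index, N would stay near 11,410, but a frailty for facility alone would ignore repeat episodes within a patient.

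**Conclusion.** Wrong as written, with limited consequence. The 92% is an upper figure for 11,410: it counts episodes as patients and ignores the end of surveillance. Counting each patient once lowers it by about 4-6 points, to 86-88%, assuming a constant hazard, 15-19% repeat episodes and full 6-month follow-up less the stated 10% loss. The further fall to about 80-83% or 76-79% is conditional on surveillance ending at the 12-month minimum, in the post period or in both. No single replacement figure follows from the document alone. The point concerns the HR 0.9 column of one secondary endpoint; the primary endpoint of Stage 2 is planned on precision and is not affected.

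**What to change.** In section 4.2.1, under S2.SE17 and Table 3:

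- convert Table 1's episodes to distinct patients and use one unit label throughout;
- enter staggered enrolment and the actual surveillance end date;
- make N match the population that 9.2 analyses;
- restate the HR 0.9 column with its assumptions shown (for 11,410, about 86-88% with full follow-up, lower if truncated).

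In section 9.2, take the first eligible episode per patient per period as the index. Use the routine surveillance data to count re-presentations up to 6 months after the last index episode, which removes the truncation loss.

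The cost is one recalculated table, two sentences and a somewhat less favourable stated power in one column. Surveillance is already continuous, so where it goes on past the last index visit no new data collection is needed.
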